#### Mixed methods assessments

We will analyze the findings from mixed methods assessments using the normalization process theory to gauge potential sustainability of the interventions [30].

The Baseline Assessment Tool and Readiness Assessment Form, administered pre-implementation, will be analyzed to identify any significant differences at baseline. At endline analysis, we will assess the association between pre-implementation preparedness and the primary outcomes of the intervention. The Baseline Assessment Tool will yield a mix of continuous variables (e.g., number of health workers) and dichotomous variables (e.g., availability of equipment). Meanwhile, the Readiness Assessment Tool will provide an average Likert score for variety of parameters related to readiness, as ranked by the groups of stakeholders who complete the form for each facility.

The IDIs and FGDs are primarily designed to assess the key stakeholder views’ on the project’s implementation, including perceived successes and challenges and reasons for each. Content analysis of the IDIs and FGDs will be done using qualitative analysis software. From the acceptability-appropriateness-feasibility survey, average Likert scale scores for acceptability, appropriateness, and feasibility will be calculated for each facility and each model. Any large variations across the types of respondents will be noted. Qualitative data will be triangulated with quantitative data to provide explanations for facilities scoring below or above average on these assessments. A trend graph of acceptability and feasibility aggregate scores at each phase of the project will be plotted for each health facility at the completion of the study.

Client satisfaction will be measured on the Client Exit Survey using Likert scales and open-ended questions. Clients who score at least an average of 4 on the Likert scale will be classified as satisfied, and proportion of satisfied FP and CCSPT clients will be calculated for each facility. Responses to the open-ended questions will be analyzed using inductive thematic content analysis to provide explanations for clients’ satisfaction or non-satisfaction.

We will assess any changes from baseline in the service providers’ workload by estimating the daily client-to-provider ratios and reviewing self-reported assessment of the providers’ workload on the workload assessment tool. Findings from the Workload Assessment Tool will provide context for variations in the uptake of CCSPT and FP and will help us understand how non-CCSPT services have been affected at the facility by the introduction of our CCSPT intervention.

On a regular basis, the project staff will observe facility staff as they deliver CCSPT and FP services and will record adherence to protocols using the Observation Checklist. Staff will be aware of the presence of observers and instructed to continue performing duties as they ordinarily would; the observations are intended to be overt and non-participatory. Facilities will be graded in the poor, average, or well-performing categories based on the average scores from observations of their staff. We will compare the scores across time points, facilities, and models.

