## Methods/design

### Aims and objectives

Our aim is to compare the effectiveness, acceptability, appropriateness, feasibility, and budget impact of integrating self-sampled HPV testing into FP services via clinics only versus including community-based screening.

Our specific objectives are as follows:
Compare the effectiveness of our two models on uptake of CCS and FP services among eligible women in the catchment areas of health facilities assigned to the two models. The effectiveness will be evaluated through analysis of an Endline Household Survey, which will be administered to randomly selected eligible women in the catchment areas of the health facilities at the end of project implementation.
We hypothesize that the proportion of eligible women who have received CCS services during the 12 months of project implementation will be higher among eligible women in the catchment areas of health facilities assigned to model 2 than in model 1.We hypothesize that the proportion of eligible women who have received FP services during the 12 months of project implementation will be higher among eligible women in the catchment areas of health facilities assigned to model 2 than in model 1.Assess the acceptability, appropriateness, and feasibility of the two models among key stakeholders, including providers, facility management teams, and clients. These implementation outcomes will be evaluated through analysis of mixed methods assessments, including use of quantitative tools (Acceptability-Appropriateness-Feasibility Tool, Client Exit Survey) as well as qualitative interviews with providers, facility management teams, and clients.
We hypothesize that both models will be viewed as acceptable and appropriate by health care providers, facility management teams, and clients.We hypothesize that both models will be feasible in a variety of health facilities in Malawi.Estimate the cost and budget impact of each model compared to the standard-of-care (VIA and cryotherapy). These outcomes will be evaluated through analysis of structured observations during time-and-motion studies, the Workload Assessment Tool, and cost expenditures during implementation of the study.
We hypothesize that both models will be more cost-effective than the current standard-of-care for the number of cervical cancer case averted.We hypothesize that model 1 will be more cost-effective than model 2.

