Manager and coordinator in-depth interviews (IDIs)	Interviews assess facility managers’ and coordinators’ attitudes towards project implementation.	Facility managers and coordinators currently working at one of the 16 facilities	24 participants (3 from Zomba and 3 from Lilongwe each, at 4 time points)
Provider and HSA focus group discussions (FGDs)	Focus group discussions address providers’ and HSAs’ attitudes towards project implementation, including barriers, facilitators, successes, and challenges.	Providers currently working at one of the 16 facilities; includes HSAs at facilities randomized to community model	16 FGDs, 2 FGDs per district (1 with providers, 1 with HSAs) at 4 time points
Acceptability-Appropriateness-Feasibility tool	This survey is completed by the officer-in-charge and 2 providers at 4 time points and asks participants to rank acceptability, appropriateness, and feasibility of project activities using Likert scales.	1 officer-in-charge and 2 providers from each of the 16 facilities at each time point	Up to 192 forms (up to 48 participants per 4 time points)
Client in-depth interviews (IDIs)	Interviews assess clients’ attitudes towards project implementation, including the acceptability of self-collection and of CCSPT/FP integration.	Clients who participated in cervical cancer screening via self-collection at one of the 16 facilities during the study period	32 participants (16 who were screened at facility and 16 who were screened in community)
Client Exit Survey	This survey includes a 5-point Likert scale to measure clients’ opinions and perceptions on quality of CCSPT and FP services.	Clients who accessed CCSPT and FP services at the facilities	Up to 2370 participants (790 participants each at 3 time points, with the number of participants interviewed per facility proportional to the number of FP clients at that facility)
Workload Assessment Tool	This survey asks providers and lab staff to self-assess their workload.	Providers, HSAs, and lab staff	240 participants (5 per facility per 3 time points)
Observation checklist	Structured observation of providers and lab staff to assess fidelity to project protocols.	Providers and lab staff	Up to 1152 checklists (one per facility per week)
Objective 3: Estimate the cost and budget impact of each model compared to the standard-of-care (VIA and cryotherapy).			

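### Client satisfaction is reduced to a yes/no cut at an average Likert score of 4, and no summary of the score itself is named, although the models are to be compared on acceptability (minor point)

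*Protocol article*

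**What the plan says.** Table 2 of the protocol article describes the Client Exit Survey: "This survey includes a 5-point Likert scale to measure clients’ opinions and perceptions on quality of CCSPT and FP services". Its size is given as "Up to 2370 participants (790 participants each at 3 time points", shared among facilities in proportion to their family planning clients.

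The analysis plan (Mixed methods assessments) fixes the handling of the score: "Clients who score at least an average of 4 on the Likert scale will be classified as satisfied", after which the "proportion of satisfied FP and CCSPT clients will be calculated for each facility". Open-ended answers are analysed thematically "to provide explanations for clients’ satisfaction or non-satisfaction". No mean, distribution or per-model summary of the client score is named, and no reason is given for the cut.

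Other scored tools keep their scores. For the tool completed by officers-in-charge and providers, "average Likert scale scores for acceptability, appropriateness, and feasibility will be calculated for each facility and each model". The readiness form also yields average Likert scores. Observation results are graded into categories, but the scores are also to be compared over time points, facilities and models.

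On purpose, the Aims and objectives section states: "Our aim is to compare the effectiveness, acceptability, appropriateness, feasibility, and budget impact of integrating self-sampled HPV testing into FP services", for clinics only against clinics plus community screening. Objective 2 lists the Client Exit Survey among its quantitative tools.

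**The concern.** Each client supplies an average on a 1-to-5 scale. After the cut, an average of 3.9 counts the same as 1, and 4.0 the same as 5. A shift in opinion that stays on one side of 4 does not show, whether it lies between models or between the three survey rounds.

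In Table 2 this survey is the only quantitative rating of the services by clients. The client interviews are qualitative, and the EQ-5D-3L measures health. If the models are to be compared on client acceptability, this is the number that would be used. It rests on modest samples per facility and seven randomised facilities per arm, so avoidable imprecision matters.

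**Working it through.** **The plan's own figures.** 790 × 3 = 2370, as stated. Over 16 facilities, 790/16 = 49.4 clients per facility per round on average. The documents give no mean, SD, proportion satisfied, ICC or power for satisfaction. The one power figure for the final design (at least 83%, 40% v 70% screened, 7 facilities per arm, ICC 0.15, coefficient of variation 0.35, 3400 women per cluster) concerns screening uptake. It reproduces closely. The design effect is 1 + (1.1225 × 3400 − 1) × 0.15 = 573.3, the standard error is √[0.45 × 573.3/(7 × 3400)] = 0.104, and power is Φ(0.30/0.104 − 1.96) = 82%, with two-sided 5% assumed. It says nothing about satisfaction, but the same section supplies ICC values that can serve as a range: 0.12–0.19 for planning and 0.004–0.20 in the studies it cites.

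**Assumptions.** Normal client score; proportion satisfied p between 50% and 90%; 49 clients per facility per round; ICC ρ from 0.004 to 0.20.

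**Single facility.** Let z be the normal quantile of p and φ the normal density. For a small shift in the score, the efficiency of the proportion relative to the mean is φ(z)²/[p(1−p)].

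| p | Efficiency | Loss | Equivalent clients out of 49.4 |
|---|---|---|---|
| 50% | 0.1592/0.25 = 0.64 | 36% | 31 |
| 80% | 0.0784/0.16 = 0.49 | 51% | 24 |
| 90% | 0.0308/0.09 = 0.34 | 66% | 17 |

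The between-facility ICC does not enter here. At p = 80% the 95% interval for one facility's proportion is about ±1.96 × √(0.8 × 0.2/49.4) = ±11 percentage points.

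*Check on normality.* Simulated averages of 1, 5 or 10 five-point items, with assumed thresholds and item correlation and 41–93% satisfied, gave losses of 29–62%.

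**Comparison of models.** Facilities are the randomised units, so variation between them enters both measures. With m clients per facility:

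- Variance of a facility mean, in units of the client SD: ρ + (1−ρ)/m.
- Variance of a facility proportion on the same scale: p(1−p)[r + (1−r)/m]/φ(z)². Here r is the ICC of the yes/no variable, r = [Φ₂(z,z;ρ) − p²]/[p(1−p)], and Φ₂ is the bivariate normal distribution function.
- Loss: 1 minus the first divided by the second.

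Example with ρ = 0.15, p = 0.8, m = 49, which gives r = 0.0774. The first is 0.15 + 0.85/49 = 0.1673. The second is 0.16 × (0.0774 + 0.9226/49)/0.0784 = 0.196. The loss is 1 − 0.1673/0.196 = 15%.

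| ICC | p = 50% | 70% | 80% | 90% |
|---|---|---|---|---|
| 0.004 | 32% | 38% | 47% | 62% |
| 0.05 | 14% | 18% | 24% | 37% |
| 0.12 | 8% | 11% | 16% | 27% |
| 0.15 | 7% | 10% | 15% | 26% |
| 0.20 | 6% | 9% | 14% | 25% |

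The number of clients also matters. At ICC 0.12–0.20 the loss is 13–43% with 16 clients per facility. It is about 3–18% with 148, which is roughly all three rounds pooled (2370/16).

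**The case against.** Several objections have force.

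- **No test is described.** The plan states no between-model test, effect size or power for client satisfaction, and satisfaction is not among the key outcomes of the household survey. The specific hypothesis is that both models are acceptable, and the share of clients at or above a fixed scale point answers that fairly directly. This stands, and it makes the point minor. It does not remove it, because the stated aim is comparative and the Discussion gives a direction.
- **The score is not lost.** A reader might infer that the proportion is all that will ever be reported. The article does not say so. Each client's average must be computed before it is classified, nothing excludes reporting means, and a fuller protocol or analysis plan may do so. What the article does fix is the cut and the one numerical summary it names.
- **The difference from the provider tool may be deliberate.** That tool has three respondents per facility per round, too few for a useful proportion, and it measures other constructs. The contrast shows that scores are retained elsewhere in the plan; it is not in itself an error.
- **The cut is simple and prespecified.** It is a whole scale point, and the classification also serves the thematic analysis. That is a reason to keep the proportion, but not a reason to leave out the score.

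**Conclusion.** The concern holds as a minor point on a secondary implementation outcome. Under a normal score with 50–90% satisfied, the cut loses about 36–66% of the information in one facility's estimate.

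A reader might carry that range over to the comparison of models. The documents do not support this, because facilities are randomised and between-facility variation dilutes the loss. With 49 clients per facility it is about 32–62% at an ICC of 0.004, 14–37% at 0.05 and 6–27% at 0.12–0.20. Which range applies is unknown: the planning ICC was set for screening uptake, and none is given for satisfaction. A statement that the trial loses a given amount of power on satisfaction would refer to a test that the article does not contain. The primary result is unaffected.

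**What to change.** In the analysis plan under Mixed methods assessments, add that each client's average Likert score will be summarised as a mean with a confidence interval by facility, survey round and model. Base any contrast between models on these scores over the 14 randomised facilities, allowing for facility clustering and for the small number of clusters, as already planned for the household survey. Keep the proportion scoring at least 4 as a descriptive companion, so that the satisfied/not satisfied reading and its link to the open-ended answers remain.

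The change is a sentence or two of analysis wording. It needs no new data, clients or staff, and its only downside is one additional summary to report.

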#### Cost and budget impact

For the CCSPT intervention proposed, we will calculate the incremental cost of the two models (including both costs incurred and averted), the cost per woman screened, and the cost per cervical cancer case averted. We will also estimate the cost per use of CCSPT and FP services. Cost data will be used to conduct a budget impact analysis from the Malawi MoH perspective.

Micro-costing studies will use the time and motion evaluations, routine service utilization data, study budgets, workload assessments, structured observations, and client exit surveys. Estimated costs will also be abstracted from published government reports and the health economics literature, based on methods from published cost-effectiveness research [31, 32]. Costs will be compared between the two models and between each model and the current standard of care (VIA and cryotherapy). The number of women screened will be based on the results of the Endline Household Survey.

To estimate the impact of HPV screening and treatment, we will use a decision analysis model to simulate HPV infection, clearance, persistence, and progression to high-grade cervical intraepithelial lesion and cancer (CIN2+), informed by previous modeling work [33, 34]. Our modeling will also capture differences in cost and outcomes by HIV status.

For budget impact analysis, we will consider direct program costs, to ensure that measurements of MoH costs reflect the opportunity cost of the resources used in delivering services. The primary analysis will be from the programmatic perspective, the point of view of decision makers. A secondary analysis will be presented from the societal perspective, using data on economic productivity for disease averted and costs of accessing services.

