## Background

Cervical cancer is largely preventable through screening and preventive treatment (CCSPT), yet it remains the leading cause of cancer cases and cancer deaths among Malawian women [1]. Resource-limited countries bear a disproportionate share of global cervical cancer burden: incidence and mortality are two to four times higher in resource-limited countries compared with the highest-resource countries [2]. However, innovative methods for screening and treatment offer increased opportunities to scale-up CCSPT in resource-limited countries.

Malawi introduced a national CCSPT program in 2004 to work towards a national screening rate of 80%, but its reach has been limited. As of 2015, only 26.5% of women had been screened at least once in their lifetime, and only 43% who screened positive received appropriate treatment [3]. The currently used primary screening strategy (visual inspection with acetic acid or VIA) requires a time-consuming pelvic examination, which is challenging to offer for large scale screening because of limited clinic space at health facilities and limited numbers of providers. Timely preventive treatment of screen-positive women is also difficult to achieve because cryotherapy, the currently used ablative treatment, requires relatively expensive and heavy refrigerant gas cylinders [3]. Many of these barriers apply in other resource-limited settings beyond Malawi.

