Since the implementation of Malawi’s CCSPT program, the World Health Organization (WHO) now recommends human papillomavirus (HPV)-based screen-and-treat programs where feasible [4]. HPV assays have improved sensitivity over VIA, although with somewhat lower specificity for the detection of high-grade cervical dysplasia [5, 6]. Newer HPV assays allow for results within hours and perform similarly whether a self-collected or provider-collected cervicovaginal sample is used. Self-sampling can remove key bottlenecks for screening because it eliminates the need for a provider and an examination table for initial screening and may be more acceptable to women than physician sampling [7]. A meta-analysis of 34 studies showed that offering self-sampling increased screening uptake compared to standard-of-care, though most of the studies were from high-resource countries [8]. HPV viral DNA remains stable on dry cervicovaginal swabs up to a month after collection [9, 10], which allows delayed testing of self-collected samples and opens up the opportunity for community-based screening, which is especially important for women in rural areas.

Meanwhile, thermal ablation provides a less resource-intensive method for treating screen-positive women. Similar to cryotherapy, thermal ablation is simple to learn and can be performed by mid-level providers, but it does not require heavy gas cylinders and is available through hand-held portable devices. Early experience suggests that thermal ablation has high cure rates, similar to cryotherapy and loop electrosurgical excisional procedures (LEEP) [11, 12]. Some facilities in Malawi have already pivoted to using thermal ablation due to the difficulties with maintaining functioning cryotherapy machines [3, 13].

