### Setting

This study will occur in two districts in Malawi: (1) Lilongwe in the Central Region and (2) Zomba in the Southern Region. It is unknown how cervical cancer incidence differs across the country, but regional variation in HIV prevalence suggests that there is likely variation in cervical cancer burden, since HIV infection greatly increases risk for persistent HPV infection and cervical cancer development [20]. HIV prevalence among women aged 15–49 is 10.8% nationally, 6.7% in the central region, and 15.7% in the southern region [21]. Without knowledge of how cervical cancer and HPV infection vary geographically, selecting districts from two different regions helps ensure better representativeness.

Malawi is a country of 18.1 million people in southeastern Africa. Gross domestic product (GDP) is $516 USD, among the lowest in the world [22]. Health care facilities in Malawi are operated by the Ministry of Health (MoH), the private for-profit sector, and the Christian Health Association of Malawi (CHAM), which is Christian-affiliated and heavily publicly subsidized [23]. In most facilities regardless of sector, service utilization data is recorded in standardized MoH registers. The MoH organizes regular surveillance of facility service utilization by having facilities submit monthly reporting forms to District Health Offices [23].

HSAs in Malawi comprise 30% of the health care workforce [23]. Originally, HSAs focused on immunizations and health education, but their role has since been expanded to clinical activities such as pediatric disease management, HIV testing, and FP provision [24]. HSAs typically deliver services in community outreach or village clinics, which are held in a given location anywhere from several times a week to once every few weeks. Some HSAs are utilized to provide basic care in health facilities or to provide home visits. The minimum qualifications for an HSA are a secondary school certificate and completion of a 12-week MoH-administered HSA training program [24].

In 2015, there were 130 public health facilities providing VIA and one providing Pap smear [3]. For treatment, 32 public facilities provided cryotherapy, though the machines were only functional at 22, and 11 offered thermal ablation. More sites have likely added thermal ablation since 2015, since thermal ablation was only introduced in the country in 2013 and added to the National Cervical Cancer Control Strategy in 2016 [13].

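### The cost comparison fixes current standard of care as VIA and cryotherapy, while the article itself describes a mixed practice in which some facilities already use thermal ablation

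*Protocol article*

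**What the plan says.** Objective 3 under Aims and objectives reads "Estimate the cost and budget impact of each model compared to the standard-of-care (VIA and cryotherapy", and the Objective 3 heading in Table 2 names the same comparator. The Cost and budget impact part of the Analysis plan repeats it and calls it current: "Costs will be compared between the two models and between each model and the current standard of care (VIA and cryotherapy". One hypothesis rests on this comparator, namely that "both models will be more cost-effective than the current standard-of-care for the number of cervical cancer case averted". The Background supports the choice by referring to "cryotherapy, the currently used ablative treatment".

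Two other places give a different picture of current practice. Later in the Background: "Some facilities in Malawi have already pivoted to using thermal ablation due to the difficulties with maintaining functioning cryotherapy machines". Under Setting, for 2015: "32 public facilities provided cryotherapy, though the machines were only functional at 22, and 11 offered thermal ablation". The same paragraph adds: "More sites have likely added thermal ablation since 2015, since thermal ablation was only introduced in the country in 2013". It also records that thermal ablation entered the national strategy in 2016. The protocol version presented is dated September 2019 (Ethical considerations).

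Both models combine HPV self-sampling with thermal ablation. Neither trial arm delivers the standard of care, so the standard-of-care side of Objective 3 has to be built from costing data, literature and the decision model.

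**The concern.** Relative to the named comparator, the models change two things at once: the screening test (VIA to self-sampled HPV testing) and the ablation device (cryotherapy to thermal ablation). If part of the country had already made the second change, a comparator that contains only cryotherapy is not what the Ministry of Health would have without the models. The estimated increment then includes some change in cost or access that was under way regardless.

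This matters because the stated aim concerns integrating self-sampled HPV testing into family planning services, and the Discussion ties continuation to funding for HPV cartridges. A budget holder would want to know what the HPV component adds to existing practice. With a single cryotherapy-only comparator, the result does not show how much comes from the test and how much from the device.

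**Working it through.** The article states no figure for this comparison, so there is none to reproduce. The check sets the statements side by side, does arithmetic on the 2015 counts, and works out what the choice of comparator does to the increment.

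**Inputs (Setting, 2015, public facilities).** Cryotherapy offered at 32, functional at 22; thermal ablation offered at 11. The overlap between the 22 and the 11 is not given; call it k, from 0 to 11.

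**Step 1. Working cryotherapy.** 22/32 = 69% functional, so 10/32 = 31% not functional.

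**Step 2. Sites with working ablation that had thermal ablation.** The number of sites with any working ablation is 22 + 11 − k = 33 − k, taking the 11 thermal sites as working.
- Share with thermal ablation = 11/(33 − k).
- k = 0 (no overlap): 11/33 = 33%.
- k = 11 (full overlap): 11/22 = 50%.

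**Step 3. Sites with thermal ablation and no working cryotherapy.** Share = (11 − k)/(33 − k).
- k = 0: 11/33 = 33%.
- k = 11: 0/22 = 0%.

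The 50% in Step 2 therefore corresponds to thermal ablation standing beside cryotherapy everywhere, not replacing it. Both steps count sites offering a device, not women treated.

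**Step 4. Effect on the increment.** Let p be the share of current treatment delivered by thermal ablation. Let C_cryo and C_th be the programme costs under VIA with cryotherapy and VIA with thermal ablation, and C_m the cost of a model.
- Increment against cryotherapy only: C_m − C_cryo.
- Increment against the mix: C_m − [(1 − p)C_cryo + p·C_th].
- First minus second: p(C_th − C_cryo).

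The same algebra gives p(E_th − E_cryo) for cases averted. The distortion is zero if p = 0 or if the two devices give the same programme cost and effect.

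**Step 5. What the article says about these terms.**
- p is not given. Site counts suggest it is above zero, and growth since 2015 is described as likely but not quantified.
- E_th − E_cryo: cure rates are reported as similar, so any difference has to come through equipment function, access and completion of treatment.
- C_th − C_cryo: the article describes thermal ablation as less resource-intensive and notes the expense of gas cylinders, which suggests a lower cost per treatment. Better access would mean more women treated, which raises programme cost. No unit costs are given.

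The sign and size of the effect on cost per case averted therefore cannot be obtained from the article.

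**The case against.** The strongest reply is that thermal ablation is part of the intervention. The Abstract and Background present the programme as HPV self-sampling plus thermal ablation set against VIA plus cryotherapy, and Objective 3 does not promise an effect of self-sampling apart from the device. This stands: crediting the package with its own components is the declared comparison. It does not cover the share of thermal ablation already in routine use, which belongs on the comparator side.

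A second reply is that the shift is partial. Only some facilities are said to have switched, cryotherapy sites outnumbered thermal sites in 2015, and study facilities may go on offering VIA and cryotherapy. This also stands. A reader might infer that the comparator is obsolete because cryotherapy had been replaced. The article supports a mixed and changing practice, not replacement.

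Third, the site shares do not measure bias. A reader might infer that cost per case averted will be wrong in favour of both models, or that the cost-effectiveness hypothesis is too easy to meet. The article does not support either inference, for the reasons in Step 5. The one treatment-completion figure for the existing programme, 43%, is given for 2015 and cites the same source as the site counts. If that figure feeds the model, it may already reflect mixed practice. The article does not say whether it does.

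Fourth, scenario detail is commonly left to a fuller protocol or economic plan that is not shown. That is fair, and the absence of scenarios is not the point. The point is that the comparator is stated three times and does not fit the article's own account of current practice.

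**Conclusion.** The concern holds in a limited form. The comparator called current conflicts with the Background and Setting statements on thermal ablation. A base case containing cryotherapy alone would credit the models with any cost, equipment or access change from thermal ablation that was already in routine use.

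The only size available is the 2015 presence of thermal ablation at 33% to 50% of public sites with working ablation. It assumes that all 11 thermal sites were working and that overlap lies between none and full. It describes availability, not bias.

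The point is confined to the standard-of-care comparison in Objective 3. The primary uptake outcome and the model 1 versus model 2 comparison are untouched, because both models use thermal ablation. It concerns the analysis comparator only and implies no view on which treatment should be used.

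**What to change.** Reconcile the descriptions of standard of care in the Background, Objective 3, Table 2 and the cost section of the Analysis plan with the account of thermal ablation in the Background and Setting.

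- **Base case.** Define the comparator as VIA with the ablation mix in actual current use, including sites with none functional. Draw the mix from baseline facility data together with national programme data, and state the source and how representative it is. Study facilities alone may not suffice: they were chosen with the district teams, assessed for readiness, and excluded if they lacked family planning services or a laboratory. The Baseline Assessment Form covers screening and treatment capabilities and equipment availability, but the article does not say that it records the ablation method, so this needs checking.
- **Scenarios.** Keep VIA with cryotherapy and add VIA with thermal ablation as comparators in the planned decision model. The second isolates the increment from HPV self-sampling; the difference between the two shows the increment from the device.

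The cost is a little more modelling work and possibly a less favourable cost-effectiveness figure. No new arm is needed.
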